## 4. Statistical Considerations

### 4.1. Sample Size

One hundred and sixty patients on hemodialysis are needed to address the study hypothesis. The sample size was established on pragmatic grounds by considering the statistical models that will be applied to address the study hypothesis [i.e., the linear mixed models (LMM) analysis or generalized estimating equations (GEE)]. In this case, a total of 640 observations over the time period will be collected in 160 patients, thus ensuring adequate power to adjust for major potential confounders.

### 4.2. Data Analysis

Normally distributed variables will be summarized as means and standard deviations, non-normally distributed variables as medians and interquartile ranges, and categorical data as absolute numbers and percentages. At baseline, the between-groups comparisons will be performed using the independent *t*-Test, the Mann–Whitney U Test, or the Chi-squared test, as appropriate. The between-groups comparisons of repeated measurements of biomarkers (as continuous variables) over time will be performed by linear mixed models (LMM) or generalized estimating equations (GEE). No imputation method of missing values will be applied. In these analyses, the effect of the exposure to Etelcalcetide in treated patients versus those untreated will be preliminarily investigated by including the group variable, the time, and the interaction term between the group variable and time. The effect of potential confounders on the effectiveness of Etelcalcetide on the study outcomes will be further investigated by adjusting for all potential confounders, including medications, by multiple regression models. Sensitivity analysis by applying the propensity score approach will be also performed. The primary analysis will be conducted considering the patients as belonging to the treatment arm they had at the beginning of observation. A secondary analysis will also be performed taking into account any cross-over. Survival analyses will be performed using the Kaplan–Meier and Cox regression methods. All statistical analyses will be performed using a standard statistical package (STATA 16, StataCorp. Stata Statistical Software. College Station, TX, USA).

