## 2. Methods

### 2.1. Study Design

This is a national, multi-center, comparative effectiveness, observational, longitudinal study with no predefined interference on drug dosing by the investigators. Nineteen Italian centers will be involved. In each center, 14 patients will be screened for eligibility and about 10–12 patients are scheduled to be enrolled. This study will enroll 160 hemodialysis patients (80 patients treated with Etelcalcetide and 80 age- and sex-matched patients treated with calcitriol or a vitamin D analog, paricalcitol) (Figure 1).

Given the observational nature of this study, the investigators will not recommend target goals of Etelcalcetide treatment. The treating nephrologists will tailor their target dose of Etelcalcetide on an individual-level patient basis in order to achieve the KDIGO PTH target levels. In the Etelcalcetide-treated group, the addition of calcitriol is allowed when required by current clinical practice (for correction of hypocalcemia). Blood samples for the measurement of specific biomarkers will be collected in concomitance with the routine blood sampling scheduled in each center. At baseline, all relevant demographic, clinical, and biochemical data will be collected in compliance with the privacy laws of the European Union. The study design is illustrated in Figure 2.

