## 3. Study Objectives and Aims

### 3.1. Main Outcome Measures

The main outcome measure is the comparison of VKDP levels between patients treated with Etelcalcetide and those treated with vitamin D or vitamin D analogs. The longitudinal changes of the following VKDPs (measured at baseline and after 3, 9, and 18 months) will be compared between the two groups: total MGP, dephosphorylated-undercarboxylated MGP (dp-ucMGP), total BGP, and undercarboxylated BGP (ucBGP).

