7.Changes from baseline total hip, femoral, and neck bone mass density (BMD), measured by dual-energy X-ray absorptiometry (DEXA), including a trabecular bone score (TBS) when available. To test if 18 months of treatment with Etelcalcetide improves BMD and TBS.8.To assess the relationship of bone vascular biomarkers and clinical outcomes: VFs and VCs.9.To compare a novel quantitative computer-assisted scoring method for vascular calcifications with a three-dimensional assessment from CT data [12,13].10.To evaluate the effect of Etelcalcetide on cardiovascular events and all-cause mortality.11.To evaluate the safety of Etelcalcetide and drug interactions.

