### 5.1. Instrumental Data

#### 5.1.1. X-ray

According to the current indications of good clinical practice and guidelines, at baseline, the patients will undergo a lateral dorsal lumbar spine X-ray using dedicated software (Calcify 2D [13]) to evaluate vascular calcifications (VCs: aorta and iliac arteries) [12,13,14,15] and VFs, where vertebral fractures will be identified if the height of the vertebral body is reduced by at least 20% or 4 mm, according to Genant et al. [16]. Furthermore, a lateral dorsal lumbar spine X-ray will be performed at the end of follow-up at 18 months. Both VCs and VFs will be assessed independently by two physicians who are blinded to the patient’s clinical characteristics.

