### 7.1. Statistical and Methodological Issues

The study protocol rests on a solid longitudinal design, contemplating repeated measurements of specific biomarkers over time. When dealing with an observational study of effectiveness and with LMM/GEE (see Statistical Analysis) having repeated measurements over time as dependent variables, the estimation of the sample size mainly depends on the number of potential confounders to be included in the models rather than on a predefined effect of the drug. In this case, a total of 640 observations over the time period are expected to be collected [i.e., 80 patients x four longitudinal visits including baseline (n = 320 observations) in the exposed group and 80 patients x four longitudinal visits including baseline (n = 320 observations) in the unexposed group]. This high number of observations will allow us to adjust the effect of Etelcalcetide versus calcitriol or vitamin D analogs on study endpoints for both baseline and longitudinal potential confounders, thus obtaining robust and precise effect estimates. Furthermore, linear mixed models and generalized estimating equations analyses are robust methods for dealing with various patterns of missingness, an issue of particular relevance in studies of comparative effectiveness. Furthermore, since this is not an interventional study, the observational nature of the protocol will be guaranteed by inviting treating nephrologists to tailor the appropriate dosage for each patient individually, aiming to reach the KDIGO PTH target level as in everyday clinical practice. In the group receiving Etelcalcetide, calcitriol may also be added as needed according to the standard clinical approach to address hypocalcemia.

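### Kaplan–Meier applied to cardiovascular events alone would modestly overstate the 18-month risk; cumulative incidence with other-cause death as a competing event should replace it

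*Protocol article*

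**What the plan says.** Item 10 of section 3.2 (Other Outcome Measures) sets the aim "To evaluate the effect of Etelcalcetide on cardiovascular events and all-cause mortality". The two outcomes are named side by side; neither is defined further, and no composite of the two is stated.

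Section 4.2 (Data Analysis) gives the method in one sentence: "Survival analyses will be performed using the Kaplan–Meier and Cox regression methods". It does not say which outcome each method serves or how a death is handled when the outcome is a cardiovascular event. No cumulative incidence or other competing-risk method appears elsewhere in the article.

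For scale, section 2.1 states "This study will enroll 160 hemodialysis patients (80 patients treated with Etelcalcetide and 80 age- and sex-matched patients", and section 5.1.1 places the end of follow-up at 18 months. Section 3.1 makes vitamin K-dependent protein levels the main outcome, so the time-to-event outcomes are not primary.

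**The concern.** A patient who dies of another cause can no longer have a cardiovascular event. Kaplan–Meier for cardiovascular events alone treats that patient as censored, that is, as someone who could still have the event later. One minus the curve then describes a hypothetical setting without other-cause death, and only if the two risks are independent. It is not the proportion of real patients who have an event by 18 months, which is what a real-world effectiveness study would want to report.

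The population makes this more than academic. Section 3.3 requires severe hyperparathyroidism, at least moderate aortic and/or iliac calcification and at least a mild vertebral fracture. Section 5.1.3 itself links moderate or severe aortic calcification with co-morbidity to higher cardiovascular and mortality risk. The groups are not randomised, and the criteria for the exposed group include patients who do not respond to, or do not comply with, calcitriol, so competing mortality could differ between groups. Section 8 looks ahead to lower morbidity and mortality, so readers may take the curves as actual risks.

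**Working it through.** **The plan's own figure.** The only derived number is the count of repeated measurements: 160 × 4 visits = 640, and 80 × 4 = 320 per group. It reproduces sections 4.1 and 7.1 but has no bearing on events. No event rate, event count or power is given for the survival outcomes.

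**Inputs.** From the article: 80 patients per group and t = 1.5 years. Assumed, because the article gives none: constant rates of c = 5 to 25 cardiovascular events and d = 3 to 15 other-cause deaths per 100 patient-years.

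**Formulas.**
- One minus Kaplan–Meier with other-cause deaths censored: 1 − exp(−c·t)
- Actual cumulative incidence: c/(c + d) × [1 − exp(−(c + d)·t)]

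**Worked case, c = 0.15 and d = 0.10.**
- 1 − KM = 1 − exp(−0.225) = 20.15%
- Cumulative incidence = 0.15/0.25 × [1 − exp(−0.375)] = 18.76%
- Gap = 1.39 points, 7.4% relative; 80 × 0.0139 = 1.1 patients per group

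**Across the assumed range.**

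| c | d | 1 − KM | Cumulative incidence | Gap, points | Relative |
|---|---|---|---|---|---|
| 5 | 3 | 7.23% | 7.07% | 0.16 | 2.2% |
| 5 | 15 | 7.23% | 6.48% | 0.75 | 11.5% |
| 10 | 8 | 13.93% | 13.15% | 0.78 | 6.0% |
| 15 | 10 | 20.15% | 18.76% | 1.39 | 7.4% |
| 25 | 3 | 31.27% | 30.62% | 0.65 | 2.1% |
| 25 | 15 | 31.27% | 28.20% | 3.07 | 10.9% |

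The relative error is close to d·t/2 (for d = 0.10: 0.10 × 1.5/2 = 7.5%), so it depends mainly on other-cause mortality. Outside this range, at c = 20 and d = 20, the figures are 25.9% against 22.6%, 15% relative.

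**Group comparison, independent risks.** Take c = 15 in both groups and d = 5 against 15.
- 1 − KM is 20.1% in both groups and the cause-specific rate ratio is 1.00. Neither is biased as a statement about cardiovascular hazards.
- Cumulative incidence is 19.4% against 18.1%. This 1.3-point difference in actual risk does not show on the Kaplan–Meier curves.

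Now let the treated group have a cardiovascular hazard ratio of 0.7 (c = 10.5, d = 5) against control (c = 15, d = 15).
- Risk difference by 1 − KM: 20.15 − 14.57 = 5.6 points
- Risk difference by cumulative incidence: 18.12 − 14.05 = 4.1 points

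**Group comparison, dependent risks.** In a simulation with 1,000,000 patients per group, c = 15, d = 5 against 15 and a shared gamma frailty of variance 0.5, 1 or 2, a true null gives rate ratios of 1.03, 1.05 and 1.09. The corresponding 1 − KM values are 18.9% against 18.5%, 17.9% against 17.0%, and 16.2% against 14.8%.

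**Set against random error.** For c = 10 to 20 and d = 5 to 10, 160 patients yield about 21 to 40 cardiovascular events. Power (Schoenfeld formula, two-sided 5% assumed) is 0.35 to 0.59 for a hazard ratio of 0.5 and 0.13 to 0.20 for 0.7. In one group of 80 with complete follow-up, the standard error of an 18.8% risk is √(0.188 × 0.812/80) = 4.4 points, against a gap of 1.4.

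**The case against.** The strongest reply is that the article never says other-cause deaths are censored, nor that Kaplan–Meier will be drawn for cardiovascular events alone. The method would be right for all-cause mortality and also for a composite of cardiovascular event or death. An article may leave endpoint definitions and censoring rules to a full protocol or analysis plan that is not shown. This stands in part: the censoring is an inference, not a statement in the document. But the article does fix the methods, lists cardiovascular events separately from death and defines no composite. On that text, Kaplan–Meier for cardiovascular events leaves no other treatment of a competing death.

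A second reply is that the treatment-effect model needed here is already planned, because Cox regression with other-cause deaths censored is the cause-specific model. That is correct. What needs replacing is the absolute-risk estimate.

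A reader might go further and infer that a mortality difference between groups will distort the planned cardiovascular comparison. The documents do not support that. Under independent risks the Kaplan–Meier contrast and the hazard ratio both stay at the null; what differs is the cumulative incidence, a separate quantity. Distortion needs dependent risks, which the article does not quantify. Even then the null ratio moved only to 1.03–1.09 in the cases tried, and cumulative incidence or a cause-specific Cox model would not remove that dependence.

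**Conclusion.** The point holds as a minor one. Following the named methods for cardiovascular events as listed would overstate the actual 18-month risk by about 0.2 to 3 points (2% to 12% relative) and leave out any risk difference due to competing mortality. The size rests on assumed constant rates, and on Kaplan–Meier being used for cardiovascular events without death in the endpoint. The direction needs only the second condition, together with some other-cause deaths. The hazard ratio is not at fault under independent risks, although confounding remains a separate matter that section 7.3 acknowledges. The outcome is not primary, and with 160 patients random error is larger than this bias.

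**What to change.** In section 4.2, assign a method to each survival outcome:

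- **All-cause mortality:** Kaplan–Meier and Cox, as planned.
- **Cardiovascular events:** Aalen–Johansen cumulative incidence by group, with non-cardiovascular death as the competing event, in place of one minus Kaplan–Meier.
- **Treatment effect on cardiovascular events:** the planned Cox model, described as a cause-specific hazard ratio and reported beside the one for other-cause death, so that a difference in competing mortality is visible. A Fine–Gray model is optional.

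This assumes that cardiovascular death counts as a cardiovascular event; the endpoint definition should say so. If the intention was a composite of cardiovascular event or death, stating that would be enough, and Kaplan–Meier would then be appropriate.

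The cost is a few sentences and standard software commands. Each death must be dated and classified as cardiovascular or not, which a cardiovascular-event analysis needs in any case. The downside is that the reported cardiovascular risks become slightly lower. The change is best made before outcome data are examined.

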## 5. Laboratories and Instrumental Data

The following laboratory testing will be performed:As part of current clinical practice, the following routine biomarkers, such as calcium, phosphate, magnesium, ALP, PTH, 25(OH)D, Hb, Ht, PLTS, reticulocytes, Fe, ferritin, transferrin, and transferrin saturation, will be measured in each participating center.Specific bone vascular markers (which will be measured in a centralized laboratory) considered are total MGP and BGP, dp-ucMGP, ucBGP, procollagen I intact N-terminal or P1NP, C-terminal telopeptide or CTX, tartrate-resistant acid phosphatase 5b or TRAP 5bC-Terminal to Intact, bone-specific alkaline phosphatase (BSAP), fibroblast growth factor 23 or cFGF23 and iFGF23, klotho and soluble α-klotho, sclerostin and bioactive sclerostin, DKK1, fetuin-A, and Zinc.

### 5.1. Instrumental Data

#### 5.1.1. X-ray

According to the current indications of good clinical practice and guidelines, at baseline, the patients will undergo a lateral dorsal lumbar spine X-ray using dedicated software (Calcify 2D [13]) to evaluate vascular calcifications (VCs: aorta and iliac arteries) [12,13,14,15] and VFs, where vertebral fractures will be identified if the height of the vertebral body is reduced by at least 20% or 4 mm, according to Genant et al. [16]. Furthermore, a lateral dorsal lumbar spine X-ray will be performed at the end of follow-up at 18 months. Both VCs and VFs will be assessed independently by two physicians who are blinded to the patient’s clinical characteristics.

#### 5.1.2. DXA

According to the current indications of good clinical practice and guidelines [2], at baseline, measurements of total hip, femoral, and neck bone mineral density (BMD) will be assessed by dual-energy X-ray absorptiometry (DXA), including a trabecular bone score (TBS) when available. Furthermore, DXA and TBS will be performed at the end of follow-up at 18 months.

#### 5.1.3. Abdominal CT

If the physician, in the case of the presence of moderate/severe aorta VCs associated with co-morbidity with a resulting higher risk of cardiovascular and mortality events, prescribes an abdominal CT, these findings will be included in the study as data reflecting common clinical practice. In addition, a subset of patients with aorta calcifications confirmed by X-rays will undergo CT scans of the lumbar spine. According to [12], calcification will be considered to be present if an area of ≥1 mm^2^ displays a density of ≥130 Hounsfield units. The AAC score will be calculated from the takeoff of the renal artery to the bifurcation of the aorta into the common iliac arteries. The cross-section of the abdominal aorta on each slice will be divided radially into 12 segments. The abdominal aortic calcification index (ACI) will be calculated as follows: ACI = (total score for calcification in all slices)/12 × 1/(number of slices) × 100 (%). Semi-quantitative measurement of AAC on lateral X-rays will be conducted independently by two physicians who are blinded to the patient’s clinical characteristics. The general description of this study (including the types of clinical examinations and blood sampling over time) is given in Figure 2.

## 6. Preliminary Results

In a previous paper by us [7], we measured BGP and MGP levels and checked for the presence of vertebral fractures and vascular calcifications using a lateral dorsal lumbar spine X-ray through dedicated software (Optasia Medical SpineAnalyzer 4.0, version 4.0.2.19) to evaluate VFs, which were identified by a height vertebral reduction of at least 20% or 4 mm, according to Genant et al. [16]. In the same X-ray, we evaluated vascular calcifications (VCs: aorta and iliac arteries) [7] in 387 hemodialysis patients enrolled in the VIKI study. Total BGP levels were found to be twice as high in patients on calcimimetics compared to those untreated with this drug class (290 vs. 158.5 mcg/L, *p* < 0.0001), whereas total MGP levels were 19% higher in patients on calcimimetics (21.5 vs. 18.1 mcg/L, *p* = 0.04) than in the untreated group. Median total BGP levels were 29% lower in patients with one or more vertebral fractures (151 vs. 213 mcg/L, *p* = 0.0091) and 36% lower in patients with vascular calcifications (164 vs. 262.1 mcg/L, *p* = 0.0003). In non-survivors, median BGP and MGP levels were lower, but only the difference in MGP levels reached statistical significance (152 vs. 191 mcg/L, *p* = 0.20 and 15.0 vs. 19.7 mcg/L, *p* = 0.02, respectively). In another paper by our group [18], we assessed the prevalence of vitamin K deficiency and the relationship between vitamin K status, vertebral fractures, and vascular calcification in the same patient cohort. Overall, we found a relatively high proportion of patients with deficiencies in MK7 (35.4%), vitamin K1 (23.5%), and MK4 (14.5%). Of note, vitamin K1 deficiency was the strongest predictor of vertebral fractures (odds ratio [OR], 2.94; 95% confidence interval [CI], 1.38–6.26). MK4 deficiency was a predictor of aortic calcification (OR, 2.82; 95% CI, 1.14–7.01), whereas MK5 deficiency appeared to protect against it (OR, 0.38; 95% CI, 0.15–0.95). MK7 deficiency was a predictor of iliac calcification (OR, 1.64; 95% CI, 1.03–2.60). The presence of vertebral fractures was also a predictor of vascular calcifications (OR, 1.76; 95% CI, 1.00–3.08).

## 7. Discussion

In addition to its known suppressive effect on PTH, Etelcalcetide has demonstrated additional benefits in recent studies, both experimental and human. In rats, it has been shown to preserve cortical bone structure and bone strength by lowering PTH in subtotal Nx rats with established SHPT [19,20]. In humans, it has been found to improve areal bone mineral density and trabecular quality in the central skeleton, always by lowering bone turnover without affecting bone material properties, thereby reducing the risk of fractures [21,22]. A recent meta-analysis comparing various calcimimetics has shown that Etelcalcetide is the most efficacious calcimimetic agent for lowering serum PTH levels but highlighted side effects such as hypocalcemia, nausea, and vomiting. Cinacalcet ranked worst for nausea and had somewhat lower effectiveness, while Evocalcet (in use in Asian populations) had lower effectiveness for decreasing PTH levels but was associated with fewer adverse effects [23].

Ca^2+^-sensing receptors (CaSRs) are broadly expressed in the vascular system, including perivascular neurons, vascular endothelial cells (VECs), and vascular smooth muscle cells (VSMCs). Prolonged serum calcium is thought to reduce the sensitivity and expression of CaSR in arteries, thereby increasing intra-vascular Ca^2+^ concentrations through a negative feedback loop. Excess intravascular calcium gradually deposits in VSMCs and may in part lead to the transformation of VSMCs into osteoblast-like cells, leading to the formation of vascular calcification [24]. In experimental studies, overexpression of the CaSR reduced the deposition of calcium in human aortic smooth muscle cells (HASMCs) [24]. In uremic rats with secondary HPT treated with calcimimetics (R-568 or AMG 641), compared to the untreated mice, Rodriguez et al. reported that VCs were prevented and mortality was reduced in excess of what was expected from a reduction in calcium and phosphorus alone [25]. They have also ascribed a protective role to calcimimetics as they play a role in the expression of proteins that prevent the development of VCs, in particular highlighting an increase in MGP and a resulting reduction in osteoblastic gene expression markers such as BMP2 [7,25,26]. To confirm these findings, our group conducted a secondary analysis of the Vitamin K Italian (VIKI) study to assess the prevalence of vitamin K deficiency in hemodialysis patients [18] and to evaluate associations between drug consumption and VKDP levels in 387 hemodialyzed patients [7]. A previous study by us reported, in patients managed with calcimimetics compared to without calcimimetics, that total BGP levels were twice as high (290 vs. 158.5 mcg/L, *p* < 0.0001) and that total MGP levels were 19% higher (21.5 vs. 18.1 mcg/L, *p* = 0.04) [7,18]. Furthermore, Yu et al. showed lower aorta calcium content in uremic rats treated with Etelcalcetide than in paricalcitol-treated rats [27]. The precise mechanism by which calcimimetics enhance VKDP activity remains unclear.

Furthermore, recent studies have also shown that irisin, the hormone-like myokine crucial for muscle-bone communication [28], was significantly lower in hemodialysis patients compared with control subjects. Most importantly, within the group of hemodialysis patients, irisin was significantly lower in those with VCs compared to patients with no calcification [29].

